## Methods

Researchers plan for an assessor blinded two arm multicenter Randomized Clinical Trial (RCT) protocol to compare the efficacy of therapeutic exercise and an education booklet on sun exposure, nutrition and lifestyle versus therapeutic exercise and oral vitamin D supplement for CLBP patients with vitamin D deficiency at 2 months and 6 months after baseline recruitment in designated rehabilitation centers in Dhaka city.

For this potential trial, researchers will follow Standard Protocol Items: Interventional Trials 2013 (SPIRIT) guidelines, to help ensure quality of the interventional trial (
Table 1).

**Table 1. T1:** Study protocols according to SPIRIT guidelines.

Study (Status)	Teams (Preparation)			Patients (Execution)			
	Preparation & planning	Training to team	Piloting	Enroll	Study		
Time					Baseline 0	2 months	6 months
**Intervention**	×	×	×		×	×	
**Enrollment**	×		×	×			
Informed Consent	×		×	×			
Eligibility	×	×		×			
**Evaluations**							
BPI		×	×		×	×	×
Vit. D3		×	×		×	×	×
RMDQ		×	×		×	×	×

Abbreviations: BPI, Brief Pain Inventory; Vit. D3, Serum 25(OH)D; RMDQ, Roland Morris Disability Questionnaire.

### Study setting

To meet the objectives of the trial and prevent trial contamination, the experimental group interventions will take place at the Centre for the Rehabilitation of the Paralysed (CRP) and control group interventions will take place at SAIC College of Medical Science & Technology. We expect to get cases with similar geographical and baseline criteria of city dwellers having CLBP. Data collection from different sites will increase the generalizability of the study and prevent cross-contamination of data.

### Eligibility criteria

Participants will be included if they present with chronic low back pain (CLBP) of central origin, persisting for more than three months and classified under ICD-10-CM Code M54.5, with documented vitamin D deficiency defined as serum 25(OH)D3 levels below 20 ng/mL.
^
16
^ Eligible individuals must be adults aged 18 years or older, of either gender, residing or working in Dhaka city in office, industry, or corporate settings that involve static postures or desk jobs requiring at least six hours of sitting per day for an average of 22 days per month, and must provide informed consent. Exclusion criteria comprise comorbid conditions that may influence vitamin D metabolism or bone health, including rheumatoid arthritis, ankylosing spondylitis, osteomalacia, tuberculosis of the spine, or a history of osteoporotic fracture. Women over 50 years of age or those who are post-menopausal will also be excluded,
^
14
^ as will individuals with prior use of calcium or vitamin D3 supplements, resistance training, or high-impact weight-bearing activities within the past six months. Patients presenting with neurological red flags such as dural signs, positive straight leg raise test, or bowel/bladder incontinence will not be considered. Additional exclusions include current participation in another clinical study and withdrawal during the 8-week intervention period.

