## Abstract

**Background**: Chronic low back pain (CLBP) is a common musculoskeletal disorder that significantly impairs quality of life and is frequently associated with vitamin D deficiency. Therapeutic exercise is a cornerstone of management, yet the optimal adjunct intervention to restore serum vitamin D levels remains uncertain. No prior randomized trial has compared oral vitamin D supplementation with lifestyle education on sun exposure, nutrition, and physical activity, both combined with therapeutic exercise. We hypothesize that therapeutic exercise plus an education booklet (TEB) may be superior to therapeutic exercise plus oral vitamin D supplementation (TED) in reducing pain and disability while improving serum vitamin D levels.

**Methods**: This assessor-blinded, two-arm, multicenter randomized controlled trial (RCT) will be conducted in hospitals and rehabilitation centers in Dhaka city, Bangladesh. Adult participants (18–65 years) with CLBP and confirmed vitamin D deficiency will be recruited and randomized to either TEB or TED groups. Both groups will receive standardized therapeutic exercise protocols. The intervention duration will be 6 months, with assessments at baseline, 2 months, and 6 months. Primary outcomes include pain intensity measured by the Brief Pain Inventory (BPI) and serum 25(OH)D3 levels. Secondary outcomes include disability assessed by the Roland-Morris Disability Questionnaire (RMDQ). Statistical analysis will follow the intention-to-treat principle, using repeated measures ANOVA to compare group differences over time.

**Discussion**: This trial will provide evidence on whether a multidimensional lifestyle-based education approach combined with therapeutic exercise offers greater benefit than vitamin D supplementation with exercise in CLBP patients with vitamin D deficiency. The findings will inform clinical guidelines and support comprehensive management strategies for CLBP, particularly in resource-limited settings.

Registration: Clinical Trials Registry India (
CTRI/2022/11/047074).

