**Booklet contents (B):**
^
24–
26
^

The educational booklet provides lifestyle and self-management advice designed to complement therapeutic exercise. Key recommendations include:
•Avoid prolonged static sitting or standing; alternate between sitting and standing during work.•Consume natural sources of vitamin D3 such as milk, yogurt, fortified cereals, orange juice, mushrooms, margarine, hard-boiled eggs, and sea fish (e.g., tuna, salmon).•Engage in 30–35 minutes of sun exposure between 11:00 am and 2:00 pm.•Maintain 7–8 hours of sleep per night.•Avoid stress, smoking, and alcohol consumption, while maintaining a healthy body weight.•Perform regular physical activity as part of daily routine.

Therapeutic exercise protocol (TE):
^
27–
29
^

Both groups will receive therapeutic exercises. Exercises will focus on both back pain and disability minimization of the participants. Each session will last for 25-30 minutes, 4 days per weeks and for 8 weeks. The progression of therapeutic exercise will be as per the registered protocol. Exercises are delivered under a physiotherapist supervision and include:
•Postural advice (TH.1): Maintain erect posture in sitting and standing; avoid prolonged sitting/standing and forward bending.•McKenzie’s directional preference exercises (TH.2): Sustained positioning and repeated movements, most often extension-based, performed in sets of 10 repetitions.•Stretching exercises (TH.3): Targeting erector spinae, hamstrings, and triceps surae muscles.•Lumbar stabilization exercises (TH.4): Core strengthening to enhance spinal stability.•Weight-bearing aerobic exercises (TH.5): Jogging, stair climbing, and 30 minutes of brisk walking.•Heating modalities (TH.6): Infra-red radiation applied as adjunct therapy.

Vitamin D supplementation (D):

Participants in the TED group will receive 40,000 IU vitamin D3 capsules once weekly for 8 weeks, prescribed by a registered physician and manufactured by a licensed pharmaceutical company in Bangladesh.
^
23
^

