We expect there will be no major adverse effect for therapeutic exercise and booklet group and that there will be no request of dosage change or worsening of patients’ condition. If any of these occur we will discuss with the patient. If the patient is not willing not to continue, we will stop the intervention, and keep the data for intention to treat analysis. The vitamin D supplement group may experience some adverse effect; we will manage as per the standard measures described in the “safety measures” section. The adherence to these interventions will be monitored through checklist (Extended data 1
^
37
^). We will also monitor adverse effect using a checklist (Extended data 2
^
37
^).

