### Recruitment and study procedure

We will follow the Consolidated Standards of Reporting Trials (CONSORT) to maintain the standards of the study procedure (
Figure 1). For the initial recruitment the LBP patients attending outdoor clinics of both centers from 1st December 2022 to 30th May 2022 will be primarily screened by the outdoor team and provided participant information sheet (PIS) of the study. The final screening will be performed by two licensed physician specializing in physical medicine and rehabilitation. These physicians held postgraduate qualifications (MD/MS in Rehabilitation Medicine or Orthopedics) and had a minimum of 5–10 years of clinical experience in musculoskeletal disorders and pain management. The patient will meet the blinded assessor who will then take pretest data in a separate room, and collect a blood sample, before returning the patient to the outdoor pool. From outdoor pool, the patient will have a concealed envelop with another random ID number matched by the initial ID number given and meet the intervention provider (physiotherapist and physician or physiotherapist alone). Patient will receive the intervention provided in the written guideline enclosed in the concealed envelope. After 8 weeks of treatment completion, the patient will be further screened by blinded assessor, and another blood sample will be collected before discharge. After six months, the patient will be invited to the treatment center or visited in their house or workplace for follow up evaluation and blood sample collection. Therapeutic exercise will be provided by a graduate physiotherapist, and medication will be provided by a registered medical practitioner. Patient will pay for the physiotherapy treatment sessions but will not pay for any additional blood tests, medication or booklet.

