### Data analysis

Data will be analyzed based on its nature. Calculation and data auditing will be done using Microsoft Excel 2016. Data will be analyzed by SPSS version 23, and R-4.2.1 for Windows. Eligibility for parametric analysis will be checked using bell’s curve, skewness, kurtosis, Kolmogorov–Smirnov test and Shapiro–Wilk test. Continuous variables will be represented by using an arithmetic mean and standard deviation. Categorical data will be represented by percentage (%) and frequency. Baseline characteristics between groups will be compared using chi-square tests for categorical variables and independent t-tests or Mann–Whitney U tests for continuous variables, depending on data distribution. Normality will be assessed using the Shapiro–Wilk test. For within-group comparisons across time points (baseline, 2 months, and 6 months), repeated measures ANOVA will be applied for parametric data, with Greenhouse–Geisser correction if sphericity is violated; the Friedman test will be used for non-parametric data. Between-group differences over time will be analyzed using mixed-model repeated measures ANOVA, which accounts for group × time interactions, or generalized estimating equations (GEE) if assumptions are not met. Post-hoc pairwise comparisons will be adjusted using Bonferroni correction. Effect sizes (Cohen’s d or partial eta squared) will be reported to indicate the magnitude of differences. All analyses will be conducted at a two-tailed alpha level of 0.05, and intention-to-treat principles will be applied to handle missing data.

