### Ethical issues and informed consent

According to ethical guidelines, the researchers will abide by the Helsinki declaration. The participants' participation will be entirely voluntary, and they will have the right to withdraw from the trial at any time during the trial. The participants will be assured that participation in or withdrawal from the study will not cause any change to their regular treatment program. Participants will sign the informed consent (Extended data 3
^
37
^). The Institute of Physiotherapy Rehabilitation and Research of the Bangladesh Physiotherapy Association (BPA) has provided ethical permission (BPA-IPRR/IRB/06/16/2060) on 16
^th^ June 2022 to proceed with the study (Extended data 4
^
37
^). The trial has been registered with Clinical Trials Registry India (
CTRI/2022/11/047074) (Extended data 5
^
37
^). In case of any changes to the protocol, research team will notify to Institutional review board, the trial registry platform and in the later publications. The personal information of the participants will be confidential and stored unanimously in a dataset at the Department of nutrition and food technology at Jashore university of Science & Technology.

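### Withdrawal during the 8-week treatment is listed as an exclusion criterion; applied as written it removes randomised patients and contradicts the stated intention-to-treat analysis

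*Protocol article*

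**What the plan says.** The last sentence of Eligibility criteria reads: "Additional exclusions include current participation in another clinical study and withdrawal during the 8-week intervention period".

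Three other places address who is analysed:

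- Abstract: "Statistical analysis will follow the intention-to-treat principle".
- Interventions, closing paragraph, on a patient who does not want to continue: "we will stop the intervention, and keep the data for intention to treat analysis".
- Data analysis: "intention-to-treat principles will be applied to handle missing data".

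The timing comes from two further places. The exercise protocol fixes the treatment period: "Each session will last for 25-30 minutes, 4 days per weeks and for 8 weeks". Recruitment and study procedure places allocation before treatment: "From outdoor pool, the patient will have a concealed envelop with another random ID number matched by the initial ID number given". The patient meets the intervention provider only after that. The first assessment after baseline follows treatment: "After 8 weeks of treatment completion, the patient will be further screened by blinded assessor".

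Nowhere is the exclusion limited to a per-protocol set, or explained as meaning only that further treatment stops.

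**The concern.** An eligibility criterion has to be decidable before allocation. This one can be met only afterwards, so its only possible effect is to take out people who have already been randomised. An analyst who follows Eligibility criteria would analyse completers. One who follows Abstract, Data analysis and Interventions would analyse everyone as allocated. Both could say that they followed the protocol.

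The primary comparison would then no longer rest on the randomised groups. Completers select themselves, and the article gives reasons why that selection could differ by arm: participants and therapists are not blinded, only one arm takes capsules, patients pay for physiotherapy sessions, and the two arms' interventions are placed at different institutions. None of this shows that withdrawal will differ; it makes a difference plausible. Recruiting more patients restores numbers but does not remove such a bias.

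**Working it through.** **1. Order of events.** Baseline assessment, then the concealed envelope, then the intervention provider, then 8 weeks of treatment, then the 2-month assessment (Recruitment and study procedure; Interventions). Withdrawal during the 8 weeks therefore always falls after allocation.

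**2. The statements side by side.**

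| Place | Patient concerned | Consequence |
|---|---|---|
| Eligibility criteria | withdraws within the 8 weeks | excluded |
| Interventions, closing paragraph | unwilling to continue the intervention | intervention stops, data kept for intention to treat |
| Abstract; Data analysis | all randomised | intention to treat |

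The first row conflicts with the third for every early withdrawal. It conflicts with the second where the withdrawal consists of stopping the intervention.

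**3. The plan's own figure.** Sample size gives a minimum of 152 at α = 0.05 and 80% power, but no effect size, SD or allocation ratio, so 152 cannot be reproduced. Taking it as a total split equally (76 per arm, an assumption) and solving back with the normal approximation for two means:

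d = (1.960 + 0.842) × √(2/76) = 0.4545 SD.

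This serves only as a yardstick for the bias below.

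**4. Illustration of the bias.** All inputs here are assumed; the article gives no withdrawal rates. Let there be no true difference, let withdrawers in each arm be k SD worse than completers, and let the withdrawal proportions be p₁ and p₂. Removing withdrawers improves an arm's mean by k × p, so

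bias = k × (p₂ − p₁), in favour of the arm with more withdrawal.

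Standard error of the completer difference (SD = 1): SE = √[1/(76(1 − p₁)) + 1/(76(1 − p₂))].

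Type I error = Φ(−1.96 + bias/SE) + Φ(−1.96 − bias/SE).

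- *Lower case:* p₁ = 10%, p₂ = 20%, k = 0.5. Bias = 0.5 × 0.10 = 0.05 SD. SE = √(1/68.4 + 1/60.8) = 0.176. Ratio 0.284. Type I error = 0.047 + 0.012 = 5.9%.
- *Upper case:* p₁ = 10%, p₂ = 25%, k = 1.0. Bias = 1.0 × 0.15 = 0.15 SD. SE = √(1/68.4 + 1/57.0) = 0.179. Ratio 0.836. Type I error = 0.131 + 0.003 = 13.3%.
- *Equal withdrawal with the same k in both arms:* bias = 0, type I error 5%.

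Against the yardstick, 0.05/0.4545 = 11% and 0.15/0.4545 = 33%.

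**5. What the fix can recover.** The first outcome after baseline is taken after the 8 weeks. A patient who leaves before then and is not followed has baseline data only, whether or not the clause stands. Deleting the clause therefore helps fully only for patients who stop treatment but are still assessed. Under the stated assumptions, the figures in step 4 are an upper bound on the bias removed.

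**The case against.** The strongest reply is that the clause is a discontinuation rule in the wrong place. It stands under Eligibility criteria and does not say that data are deleted, while the sections that govern the analysis say intention to treat. That reading is possible, but the text does not state it, and the word used is exclusion. A reader might equally infer that the investigators have definitely decided to discard these patients' data; the article does not support that either. What it supports is that the rule, applied as written, has this effect and contradicts the other sections.

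Second, the Interventions paragraph and the exclusion may concern different patients. The former is about stopping the intervention after an adverse effect, a request for a dosage change or worsening. Ethical issues and informed consent speaks of leaving the trial: "they will have the right to withdraw from the trial at any time during the trial". This stands in part. The conflict with Interventions depends on withdrawal including the stopping of treatment; the conflict with the general intention-to-treat statements does not.

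Third, much of the bias from early withdrawal would persist as missing data after the clause is deleted. This stands, and it is why the figures are given as an upper bound.

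Fourth, a reader might infer a loss of power, for example by removing 15% of 152 patients. The article does not support that: Sample size calls 152 a minimum and plans extra recruitment for attrition at an unstated rate. Patients lost without outcomes would also cost power under intention to treat. No loss of power is claimed here.

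**Conclusion.** The point holds. The exclusion list contains an event that can only follow randomisation, and applying it gives a completer analysis where the Abstract and Data analysis promise intention to treat. This rests on the wording alone.

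The size is conditional. With 76 per arm, 10% versus 20-25% withdrawal, and withdrawers 0.5-1.0 SD worse than completers, the bias is 0.05-0.15 SD and the type I error 6-13%. The upper end needs both a 15-point imbalance and a full-SD gap; the lower end is close to nominal; with equal and similar withdrawal the bias is zero. A reader might infer that the trial will be biased by this amount, or that deleting the clause removes all of it. The article supports neither, since it gives no withdrawal rates and patients who are not followed remain missing.

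The clause should nevertheless be corrected before analysis, because it decides who enters the primary comparison and the correction is small.

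**What to change.** 1. Delete withdrawal during the intervention period from the exclusion list.
2. State that all randomised patients are analysed in the arm to which they were allocated.
3. State that patients who stop the intervention are still invited to the 2- and 6-month BPI, RMDQ and 25(OH)D assessments unless they withdraw consent.
4. Confine any exclusion of withdrawers to a per-protocol sensitivity analysis that is labelled as such.

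The cost is a short amendment and some additional follow-up effort for patients who stop early, within the assessment schedule already in Table 1. The article shows no budget, so that effort cannot be priced from it. If the treatment period is already over, missed visits cannot be recovered, but the analysis set can still be corrected.

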### Randomization

Researchers plan for hospital-based randomization in both study centers from 1
^st^ December 2022 to 30
^th^ May 2023 by sequential random sampling and eligibility screening. Participants were randomly assigned to either the therapeutic exercise plus education booklet (TEB) group or the therapeutic exercise plus vitamin D3 supplementation (TED) group using a computer-generated randomization sequence. Randomization was stratified by study center to ensure balanced distribution across sites. Allocation concealment was maintained through the use of sequentially numbered, opaque, sealed envelopes prepared by an independent researcher not involved in recruitment or assessment.

Blinding was implemented at multiple levels to minimize bias. Outcome assessors were blinded to group allocation throughout the study, ensuring objective evaluation of pain, disability, and serum vitamin D levels. Data analysts were also blinded to group identity during statistical analysis. Due to the nature of the interventions, participants and treating physiotherapists could not be blinded; however, strict separation between intervention delivery and outcome assessment was maintained to preserve methodological rigor.

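### Withdrawal during treatment is listed as an exclusion criterion, although it can only occur after randomisation, and this conflicts with the stated intention-to-treat analysis

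*Protocol article*

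**What the plan says.** The last sentence of the Eligibility criteria section adds two exclusions to the clinical ones: "Additional exclusions include current participation in another clinical study and withdrawal during the 8-week intervention period".

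Other parts of the protocol article bear on the same patients:

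- **Abstract:** "Statistical analysis will follow the intention-to-treat principle".
- **Interventions, paragraph on adverse effects:** for a patient who does not want to go on, "we will stop the intervention, and keep the data for intention to treat analysis".
- **Data analysis:** "intention-to-treat principles will be applied to handle missing data".
- **Recruitment and study procedure:** after screening, baseline assessment and blood sampling, "Patient will receive the intervention provided in the written guideline enclosed in the concealed envelope". The post-treatment assessment follows eight weeks later.
- **Ethical issues and informed consent:** participants are told that "they will have the right to withdraw from the trial at any time during the trial".
- **Randomization:** "participants and treating physiotherapists could not be blinded".

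**The concern.** An eligibility criterion should be decidable before allocation. Taking part in another study can be established at screening. Dropping out of treatment cannot, because treatment starts only once the envelope has assigned it. Placed among the exclusions, the clause tells the trial team to take out patients who were already randomised, while the Abstract and the Interventions section tell them to keep those patients.

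At stake is the comparison that randomisation protects. If withdrawers are taken out, the trial compares those who completed one regimen with those who completed the other. The arms could lose patients at different rates or for different reasons: participants know their treatment, one arm takes a capsule and the other follows lifestyle advice, and the protocol foresees possible adverse effects of the supplement but no major ones with the booklet. If that loss is also related to outcome, the comparisons of pain and serum vitamin D, the two primary outcomes, are biased.

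**Working it through.** **Step 1: when can the event occur?** The Recruitment and study procedure section gives the order: screening, baseline data and blood sample, concealed envelope, treatment, assessment after eight weeks. The exercise programme is described as "Each session will last for 25-30 minutes, 4 days per weeks and for 8 weeks". Withdrawal within that period therefore always comes after allocation.

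**Step 2: what happens to the patient under each meaning of withdrawal?** The Eligibility criteria section does not say which is meant.

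| Meaning of withdrawal | Eligibility criteria | Conflicting statement |
|---|---|---|
| Stops treatment | Patient excluded | Interventions: treatment stops, data are kept. Abstract: intention-to-treat |
| Leaves the trial | Patient excluded | Abstract: intention-to-treat, because a randomised patient is dropped along with data already collected |

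The clause conflicts with the article under either meaning. The Data analysis section is weaker support, because it ties intention-to-treat to missing data and not to who is analysed.

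**Step 3: how large could the bias be?** The article has no figure to reproduce here, since it states no withdrawal rate. The following is an illustration.

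Inputs:
- 76 randomised per arm: the minimum total of 152 in the Sample size section, split 1:1 (the split is assumed).
- Two-sided alpha of 0.05 (Data analysis section).
- No true difference between the arms as randomised (assumed).
- Withdrawal proportions p1 and p2 (assumed).
- Withdrawers do worse than completers in their own arm by delta, in SD units (assumed 0.5 or 1).

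Put the mean of each randomised arm at 0. If the completers' mean is m, then (1 − p)·m + p·(m − delta) = 0, so m = p·delta. The completers' difference between arms is therefore

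bias = (p2 − p1) × delta.

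Type I error is the rejection probability of a two-sample t-test from the noncentral t distribution, with noncentrality bias / √(1/n1 + 1/n2) and n1, n2 the completers in each arm. For example, for 10% versus 20% and delta 1: n1 = 76 × 0.90 = 68.4, n2 = 76 × 0.80 = 60.8, bias = 0.10 × 1 = 0.10, noncentrality = 0.10 / √(1/68.4 + 1/60.8) = 0.567, type I error 0.087.

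| Randomised per arm | Withdrawal | Completers | Bias (SD), delta 0.5 / 1 | Type I error, delta 0.5 / 1 |
|---|---|---|---|---|
| 76 | 10% vs 10% | 68.4 vs 68.4 | 0 / 0 | 0.050 / 0.050 |
| 76 | 10% vs 15% | 68.4 vs 64.6 | 0.025 / 0.05 | 0.052 / 0.059 |
| 76 | 10% vs 20% | 68.4 vs 60.8 | 0.05 / 0.10 | 0.059 / 0.087 |
| 95 | 10% vs 20% | 85.5 vs 76 | 0.05 / 0.10 | 0.062 / 0.097 |

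The last row assumes recruitment raised to 76 / 0.8 = 95 per arm. The Sample size section plans extra recruitment for attrition but gives no number. More patients leave the bias unchanged and make the test more likely to detect it.

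A simulation of 20,000 trials with 76 per arm and 10% versus 20% withdrawal gave bias of 0.049 and 0.102 SD and type I error of 0.059 and 0.089. With 15% withdrawal in both arms and delta 1, it gave bias 0.000 and type I error 0.049.

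**The case against.** The strongest reply is that this is a misplaced discontinuation rule. The Eligibility criteria section says nothing about analysis sets, and intention-to-treat is stated three times elsewhere. On that reading, treatment stops, the data stay, and nobody planned a completers' analysis. The reading is possible, but the text does not give it: the item is called an exclusion, and the article does not say which rule prevails. What stands is that removal from the analysis follows only if the clause is applied as written, and the concern is conditional on that.

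Second, the retention sentence under Interventions is narrower than it looks. It is introduced for the exercise and booklet group and for adverse effects, a requested dosage change or worsening; the supplement group is referred to the safety section. This is correct and limits that one support. The conflict with the Abstract does not depend on it.

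Third, a patient who leaves the trial may have no outcome after baseline, and handling that is a missing-data matter that an analysis plan may settle. That is fair as far as it goes, but a missing-data method can only be applied to patients who have not been excluded.

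Fourth, the rates and deficits are assumed, the effect is small in the milder cases, and the most demanding element, supervised exercise, is common to both arms. All of this stands, and it limits how much weight the figures can carry.

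**Conclusion.** The clause is wrong as written. It applies an event after randomisation as an eligibility criterion and contradicts the article's own intention-to-treat statement, whichever meaning of withdrawal is intended. This conclusion rests on the text alone and on no assumed number.

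The consequence is uncertain. It is nil if the arms lose patients at the same rate and for the same reasons. Under the assumptions above, unequal loss of 10% versus 15% or 20% gives a bias of 0.025 to 0.10 SD and a type I error of 0.052 to 0.087 from 76 per arm, and up to 0.097 from an assumed 95 per arm. The correction should be made. The document does not show that withdrawers were in fact removed from the analysis.

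**What to change.** - **Eligibility criteria:** delete the item on withdrawal.
- **Interventions:** add that patients in either arm who stop treatment stay in their assigned arm, are assessed at 2 and 6 months unless they withdraw consent to follow-up, and are included in the primary analysis. For those who withdraw consent, data collected up to that point remain in the analysis.
- **Completers' analysis:** if one is wanted, label it a sensitivity analysis.
- **If recruitment has ended:** fix this rule before unblinding, and report withdrawals by arm with reasons.

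The textual cost is one clause removed and a short addition. The practical cost is assessing patients who have stopped treatment; the article already allows home or workplace visits at six months. The estimate will include patients who did not complete treatment and may be smaller than the completers' estimate. Deleting the clause does not cure everything: retaining withdrawers reduces bias only as far as their outcomes are collected.
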